## Abstract

**Background:**

Cancer-related fatigue (CRF) is the most taxing symptom for many breast cancer patients during and after therapy. In patients with metastatic disease, the prevalence of CRF exceeds 75%. Currently, there is no gold standard for the treatment of CRF. Physical activity can reduce CRF and is recommended during and after cancer treatment, but may be too burdensome for patients with metastatic breast cancer. The aim of this study is to assess the effect on fatigue of eurythmy therapy (ERYT) compared to slow movement fitness (CoordiFit) in metastatic breast cancer patients.

**Methods:**

The ERYT/CoordiFit study is a randomized controlled, open-label, two-arm, multi-center Swiss clinical trial. A sample of 196 patients presenting with CRF will be recruited by oncologists from the departments of clinical oncology at each local study site. All participants will be randomly allocated to the intervention or control group in a 1:1 ratio. The control group is an active control intervention (CoordiFit) in order to control for potential non-intended effects such as therapist-patient interaction and participation in a program. Both ERYT and CoordiFit exercises are easy to learn, and the training sessions will follow the same frequency and duration schedule, i.e., 13 standardized therapy sessions of 45 min (once a week for 6 weeks and then once every second week) during the total intervention period of 20 weeks. The primary endpoint of the study is the change from baseline over the whole intervention period (i.e., including measurements at baseline, weeks 8, 14, and 20) in the Functional Assessment of Chronic Illness Therapy – Fatigue (FACIT-F) subscale score.

**Discussion:**

This study is the first-known randomized clinical trial assessing eurythmy therapy in the treatment of fatigue in metastatic breast cancer patients. Given the distress that fatigue causes patients, it is important to validate treatment options. If eurythmy therapy proves beneficial in CRF as part of this randomized controlled clinical trial, the study may be very impactful with implications not only for metastatic breast cancer patients but also for other cancer patients, health care personnel, scientists, and funding and regulatory bodies.

**Trial registration:**

The ERYT/CoordiFit trial was registered at the US National Institutes of Health (ClinicalTrials.gov) on July 18, 2019, #NCT04024267, and in the portal for human research in Switzerland on December 3, 2019, #SNCTP000003525.

## Introduction

Cancer-related fatigue (CRF) is the most taxing symptom for many breast cancer patients [1]. Depending on the methods used for measuring fatigue, patient group characteristics 15 to 99% of breast cancer patients experience fatigue during therapy. Also, 25 to 30% of patients continue to experience fatigue up to 5 years after completion of treatment or possibly even longer [2]. In patients with metastatic disease, the prevalence of CRF exceeds 75% [3, 4]. CRF has been shown to be the symptom that has the largest impact on quality of life [5], with negative effects on work, social activities, and daily activities [6–9]. Furthermore, CRF might lead to treatment discontinuation [2].

The pathophysiological mechanism behind CRF has not been clarified yet and is considered to be multifactorial [2, 10].

Currently, there is no gold standard for the treatment of CRF [2, 11]. The National Comprehensive Cancer Network (NCCN) Guidelines [3, 12], as well as the American Society of Clinical Oncology [13], recommend a combination of approaches. These guidelines and a recent meta-analysis [14] highlight psychosocial interventions (i.e., including education and counseling of patient and family) and physical activity as having the strongest evidence base for treating fatigue during and after cancer treatment. However, physical activity may in itself be too burdensome for metastatic breast cancer patients due to metastases or other comorbid illnesses [3]. Pharmacological treatment, including therapy with antidepressants or hematopoietic growth factors, is not recommended [2, 15]. There is increasing evidence that psychostimulants, in particular methylphenidate, are likely to benefit patients with CRF [15], but the use of pharmacological agents remains controversial [2, 3]. Finally, there is some evidence that non-pharmacological mind-body techniques (e.g., tai chi) may be effective in reducing CRF [2, 3, 11, 16–26]. So far, the available data are not sufficiently reliable to formulate final recommendations [27]. Further studies are needed to confirm the effectiveness of such interventions. Given the prevalence of CRF and the distress it causes to patients, work to advance new options to improve fatigue is highly desirable.

Eurythmy therapy has been used for more than 80 years. Eurythmy essentially consists of converting the sounds of language into movements that regulate and harmonize healing processes and thus foster recovery and regaining strength. A key aspect of the eurythmy therapy is its role in training awareness and self-perception [28–32], thus inducing physiological and therapeutic effects. Eurythmy therapy exercises are specific for a distinct medical indication, symptom, or disease [32]. In particular, for breast cancer patients, the so-called cancer series “O-E-M-L-I-B-D” is applied [26, 32].

In cancer patients, the demand for mind-body therapies has increased during recent years [11, 33–38], and breast cancer patients are more likely to use any complementary health approach than patients with other cancers [35, 39]. Eurythmy therapy has specific effects in healthy subjects, such as reducing fatigue [33] and stress [40, 41]. Moreover, studies describe a reduction of a range of symptoms [42–48], as well as improvements in quality of life [40, 48] in patients with various chronic diseases and in different target groups (i.e., children, adolescents, adults) [49, 50]. As observed with other mind-body therapies [51–55], improvements have also been described in heart rate variability (HRV) parameters (i.e., parameters that measure the adaptability of the autonomic nervous system), as well as in circadian patterns of HRV, after eurythmy therapy training [33, 56–59]. This improvement in HRV parameters relates to a change in autonomic regulation toward a more relaxed pattern and an improvement of complexity (i.e., adaptability) in the heart rate dynamics. These results suggest that eurythmy therapy might have positive effects on the autonomic nervous system. The improved relaxation may lead to better stress-coping strategies, a better circadian rhythm, and ultimately to improved quality of life. Studies generally report good compliance and satisfaction of participants and patients with eurythmy therapy [40, 50]. Finally, eurythmy therapy has been used in adults and children for several decades without any harmful effects [33, 49, 50].

The aim of this study is to assess the effect of eurythmy therapy on fatigue in metastatic breast cancer patients as compared to slow movement fitness.

## Methods/design

### Study design

The ERYT/CoordiFit study is a randomized controlled, open-label, two-arm, multi-center superiority trial. A sample of 196 female patients with metastatic breast cancer presenting with CRF will be randomly allocated to the intervention or control group in a 1:1 ratio. The control group is an active control intervention (CoordiFit) in order to control for unintended effects such as the therapist-patient interaction and active engagement (being part of a program). It consists of slow, standardized exercises that address physical coordination, stability, balance, and dexterity. These exercises are non-specific with respect to CRF and do not include mindfulness features. The study is planned to be conducted in 14 centers across Switzerland.

### Participants and recruitment

The participants will be recruited by oncologists from the departments of clinical oncology at each local study site. Our study will be advertised on the homepage of the Institute for Complementary and Integrative Medicine and flyers will be available at each study site. Subjects are only included if they meet a pre-defined FACIT-F subscale score. To avoid bothering subjects by fully informing them about a study for which they prove ultimately ineligible, a two-step consenting procedure is implemented:
Each potential participant will first be asked to sign a short “preliminary consent” form for completion of the FACIT-F questionnaire. The oncologist or a study nurse will explain to the patient briefly the nature of the study and its purpose and inform her that she might be eligible for the study depending on her FACIT-F subscale score. The preliminary consent form signed by the patient and by the oncologist or the study nurse will be documented in the patient’s source documentation.Eligible patients will then be offered to participate in the study and, if interested, will be fully informed about the trial using the full patient information and informed consent form. Written informed consent will be obtained before the participant is submitted to any study procedure. The patient has at least 24 h to consider whether to participate and can subsequently send back the signed consent form by post to the study site (a stamped, addressed envelope will be provided). A study nurse will contact the patient by phone after 6 working days if a patient does not send back the consent form. Information on the schedule of study procedures and assessments are shown in Table 1.

**Table 1 Tab1:** Schedule of enrollment, interventions, and assessments

Study period	Screening	Baseline	Intervention													Follow-up	
Time	14–1 days prior to baseline	0 (14–0 days prior to first training session)	Week 1	Week 2	Week 3	Week 4	Week 5	Week 6	Week 8	Week 10	Week 12	Week 14	Week 16	Week 18	Week 20	+ 6 months after week 20	+ 12 months after week 20
**Enrolment**																	
Preliminary informed consent for FACIT-F administration	X																
Eligibility screen	X																
Informed consent	X																
Randomization		X															
**Intervention**																	
ERYT/CoordiFit sessions			1	2	3	4	5	6	7	8	9	10	11	12	13		
**Assessments**																	
Medical history and treatments		X													X		
Patient’s Baseline questionnaire		X															
FACIT-F	X^1^								X			X			X	X	X
PSQI		X							X			X			X	X	X
PHQ-9 and GAD-7		X													X	X	X
BPI		X							X			X			X	X	X
PRFS		X													X	X	X
NCCN Distress Thermometer		X							X			X			X	X	X
Mobility of the arm		X							X			X			X	X	X
Therapist’s Questionnaire			X	X	X	X	X	X	X	X	X	X	X	X	X		
Patient diary			Every day														
Patient’s Last Session questionnaire															X		
Patient’s Follow-up questionnaire																X	X
End of Study questionnaire																	X

*BPI* Brief Pain Inventory, *FACIT-F* Functional Assessment of Chronic Illness Therapy – Fatigue, *NCCN* National Comprehensive Cancer Network, *PRFS* Patient-Reported Functional Status, *PHQ* Patient health questionnaire, *PSQI* Pittsburgh Sleep Quality Index

^1^The patient will be asked to fill in the FACIT-F questionnaire only after he returns the signed preliminary informed consent

### Inclusion and exclusion criteria for the trial

Patients who meet the following criteria will be deemed eligible for the trial: (a) female aged 18 years or older, (b) CRF according to the FACIT-F (FACIT-F subscale score < 34 [60]), (c) histologically or cytologically confirmed metastatic breast cancer, (d) Eastern Cooperative Oncology Group (ECOG) grade 0 or 1, (e) ability to physically and cognitively perform an active movement therapy, (f) ability to provide informed consent as documented by signature, and (g) ability to read, write, and speak German, French, or Italian.

Patients who meet the following criteria will be excluded from the trial: (a) inability or contraindication that would prevent prolonged follow-up, or to undergo the investigated intervention or control intervention, in the opinion of the investigator; (b) patients with psychiatric, addictive or any disorder that prevents the patient from adhering to the protocol requirements, in the opinion of the investigator; (c) significant uncontrolled cardiac disease (e.g., unstable angina, recent myocardial infarction); and (d) hemoglobin < 9 g/dl.

During the trial, all participants will continue to receive the usual care provided by their health care providers. Cancer-specific medications/treatments (e.g., chemotherapy or radiation therapy, surgery, immunotherapy, endocrine therapy) received before or during the study are documented and examined later in data analyses, but not restricted.

### Randomization

Randomization procedures were implemented at the Clinical Trial Unit of the University of Bern (CTU Bern) according to dedicated standard operating procedures. Allocation will be done by a study nurse via a dedicated website within the clinical trial management system REDCap, which also contains the electronic case report forms. All participants will be randomly allocated to the intervention or control group in a 1:1 ratio. Randomization will be stratified by center using permuted blocks with random block sizes. Only system administrators who are otherwise not involved in the trial will have access to the algorithm and stored lists during the recruitment period. The underlying randomization lists and details of the algorithm will not be disclosed but kept securely at CTU Bern. All these measures will help ensure concealment of allocation.

### Endpoints

The primary endpoint of the study is the change from baseline over the whole intervention period (i.e., including measurements at baseline, weeks 8, 14, and 20) in the Functional Assessment of Chronic Illness Therapy – Fatigue (FACIT-F) subscale.

Secondary endpoints are the following:
The change from baseline to the end of intervention (i.e., including measurements at baseline and at week 20) in the FACIT-F subscaleThe change from baseline over the whole intervention period (i.e., including measurements at baseline, weeks 8, 14, and 20) in the FACT-G, Pittsburgh Sleep Quality Index (PSQI), Brief Pain Inventory (BPI), Patient Health Questionnaire-9 (PHQ-9), General Anxiety Disorder-7 (GAD-7), NCCN Distress Thermometer, and arm mobility scores.Number of patients who return to work during the intervention phase or the follow-up.Retention will be measured by the number, period to, and reasons for attrition for each group. Compliance will be measured by the number of sessions attended, and the number of hours of home training per week.Targeted quantitative metabolomics will be investigated in 30 patients as a translational research element. Analysis of amino acids, organic acid profiles, and acylcarnitine profiles in serum and urine will be measured with high-performance liquid chromatography and liquid chromatography-mass spectrometry, allowing for analysis of over 100 metabolites. Metabolomic data will be measured at baseline and at the end of intervention (week 20).

Exploratory endpoints of the study are follow-up measurements (6- and 12-month follow-up from week 20) in FACIT-F subscale, FACT-G, NCCN Distress Thermometer, PSQI, BPI, PHQ-9, GAD-7, and arm mobility.

### Outcome measures

Fatigue and quality of life are measured using the FACIT-F. The FACIT-F belongs to the FACIT family of questionnaires developed by the original Functional Assessment of Cancer Therapy – General (FACT-G) [61, 62]. FACT-G is a patient-reported outcome measure used to assess health-related quality of life in patients undergoing cancer therapy. It assesses the impacts of cancer therapy in four primary quality of life domains: physical, social/family, emotional, and functional well-being. The FACT measurement system is a widely used measure of patient-reported outcomes in cancer research [63]. FACIT-F consists of the FACT-G plus the FACIT-F subscale comprising 13 fatigue-related items, with a total of 41 items [64]. The FACIT-F subscale assesses self-reported fatigue and its impact on daily activities and function. It has demonstrated reliability, validity, and responsiveness to change. The questionnaire is easy to read and quick to complete (about 10 min).

Sleep quality is measured using the PSQI. The PSQI is a self-rated questionnaire which assesses sleep quality and disturbances in the past 4 weeks [65]. It is currently the only standardized clinical instrument that covers a broad range of indicators relevant to sleep quality [66]. The questionnaire has shown strong reliability and moderate structural validity [66]. PSQI consists of 19 items divided into 7 component scores: subjective sleep quality, sleep latency, sleep duration, habitual sleep efficiency, sleep disturbances, use of sleeping medication, and daytime dysfunction. The sum of scores for these seven components yields one global score ranging from 0 to 21 [65]. A global score ≤ 5 is associated with good sleep quality, while a score > 5 is associated with poor sleep quality. The questionnaire is easy to complete within 5 to 10 min.

Anxiety and depression will be measured using the GAD-7 (7 items) and the PHQ-9 (9 items), respectively. Both instruments have evidence of reliability and validity [67–69].

Pain is measured using the BPI. The BPI is a 9-item self-report measure that assesses worst, least, and average levels of pain and the degree to which pain interferes in activities, mood, relationships, sleep, and enjoyment of life [70]. This measure is widely used with cancer patients and has evidence of reliability and validity [70, 71].

Patient distress is measured using the NCCN Distress Thermometer. The NCCN Distress Thermometer measures distress on a scale of zero to 10, 10 being the worst [72]. The NCCN Problem List allows patients to inform their doctor if they are having concerns in areas such as practical, family, emotional, spiritual, and physical problems. This list will not be used as part of this study in order to limit the number of questions.

The functional status of the patient is measured using the Patient-Reported Functional Status (PRFS). The PRFS is a patient-completed measure of performance status. It is the activities/function domain of the Patient-Generated Subjective Global Assessment (PG-SGA), which is a widely-used, well-validated measure used in patients with cancer [73, 74].

Factors including a patient’s socio-demographic data, time since diagnosis, stage of disease, initial metastatic breast cancer or later development, previous and current cancer therapy, co-morbidities which may cause CRF, and level of physical activity (at least once a week) are collected through tailored electronic questionnaires (medical history and treatments questionnaires and patient questionnaires) and will be taken into account for the evaluation of the effect of intervention on CRF.

### Study interventions

Both ERYT and CoordiFit exercises are easy to learn, and the training sessions will follow the same frequency and duration schedule, i.e., 13 standardized therapy sessions of 45 min (once a week for 6 weeks and then once every second week) during the total intervention period of 20 weeks. Patients are instructed by a eurythmy therapist or physical therapist, according to the group of allocation, in sessions with 1 to 4 patients. Therapists are available in all areas of Switzerland, either affiliated with institutions (e.g., hospitals) or work in private practices. Patients are asked to additionally train at home 15 min per day, 6 times a week, and compliance of the home training is reported by the patient in a diary.

All eurythmy and physical therapists will participate in an introductory teaching session before the start of the study, to familiarize themselves with the study specifics.

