#### Allocation and baseline (14–0 day(s) prior to first training session)

After obtaining the patient’s signed informed consent, the patient will be randomized and the study nurse will fill in the Medical History and Treatments questionnaire in REDCap. The study nurse will contact the patient to specify which group she has been allocated to and will answer any questions the patient may have. Then, the study nurse will contact the therapist according to the group and area of the patient and ask her to call the patient to arrange the first training session. The patient will receive via email a link (generated by REDCap) to open in a web browser the questionnaires to be filled in (i.e., Patient’s Baseline questionnaire, PSQI, PHQ-9, GAD-7, BPI, NCCN Distress Thermometer, arm mobility, and PRFS). These questionnaires constitute the baseline assessment and consequently must be filled in before the first session.

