### Sample size calculation and statistical analysis

#### Sample size

Eurythmy therapy is expected to have a greater effect on CRF than the control intervention. A validated Minimal Clinically Important Difference (MCID) for FACIT-F subscale is defined as a change in score of 3–4 points [62]. We assume a non-parallel course over time of the FACIT-F subscale score between the ERYT group and the control group and a difference ≥ 4 in the FACIT-F subscale score between the two groups at the end of the intervention (week 20).

The mean FACIT-F subscale score at baseline for the two groups was assumed to be 30 points with a standard deviation of 10 points [60]. Simulations confirmed that the sample size of *N* = 156 patients (excluding drop-outs) will provide enough power (≥ 80%) to reject the null-hypothesis of no interaction between the group and time at the *α* = 0.05 level, if the effect of the ERYT intervention on the FACIT-F subscale score at the end of therapy is 4 points, if the standard deviation of the FACIT-F subscale score is ≤ 12 points, and if the within-patient variation between two measurements is ≤ 8 points. The simulations also confirmed that the power of 80% is reached in case of slight deviations from the assumptions if the difference between groups ≥ 4 points at the end of the intervention. To account for a dropout rate of 20%, the total sample size will be *N* = 196 patients (98 per group).

In order to ensure the study population can comply with the intervention as excepted, we will check feasibility issues, i.e., the number of sessions completed and compliance with home training, after the inclusion of 50 patients.

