#### Statistical analysis

A nonparametric ANOVA model for longitudinal data, the F1-LD-F1 model of Brunner, Domhof, and Langer, will be applied to model the course of the FACIT-F subscale scores from baseline over the whole intervention [77]. The first F1 means that there is one group factor, the second that there is one-time or repeated measures factor. The main hypotheses are the following:

H0: there is no interaction of the treatment arm with the time;

H1: there is an interaction of the treatment arm with the time (favoring ERYT).

Least-square means of the original data (original scales) and 95% confidence intervals will be calculated and displayed in figures over time.

Differences from baseline to end of intervention will be analyzed by stratified Wilcoxon rank-sum tests (via ordinal logistic regression, i.e., proportional odds model with baseline measurements as co-variable, treatment arm as binary predictor and differences as outcome variable). Least-squares means of the original differences and 95% confidence intervals will be calculated.

Exploratory endpoints will be analyzed descriptively using mean and standard deviation or median and interquartile, as appropriate.

Statistical analysis will be conducted applying an intention-to-treat approach, and therefore including all randomized patients. In case of protocol non-adherence, a per-protocol analysis will be conducted to estimate the robustness of the primary estimates. All tests will be two-sided with a significance level of 0.05. Statistical analysis will be performed using R [78].

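### Patients share arm-specific therapists, but the stated sample-size inputs and the primary model carry no therapist variation; if change in FACIT-F correlates within therapist, the interaction test is anti-conservative and 156 patients count for fewer

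*Protocol article*

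**What the plan says.** Delivery, in Study interventions: "Patients are instructed by a eurythmy therapist or physical therapist, according to the group of allocation, in sessions with 1 to 4 patients". Under Allocation and baseline, after randomization "the study nurse will contact the therapist according to the group and area of the patient". Therapist is therefore nested in arm, and patients of the same arm and area can share a therapist, and sometimes a session, over 13 sessions in 20 weeks.

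Sample size: the simulations target power of at least 80% "to reject the null-hypothesis of no interaction between the group and time", "if the effect of the ERYT intervention on the FACIT-F subscale score at the end of therapy is 4 points". The other inputs are a baseline mean "assumed to be 30 points with a standard deviation of 10 points", an upper bound of 12 points on the standard deviation and an upper bound of 8 points on the within-patient variation. The result is 156 patients without drop-outs and 196 in total. No therapist or session variance is named.

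Statistical analysis: on the primary F1-LD-F1 model the article says "The first F1 means that there is one group factor"; the other factor is time. The week-20 comparison uses baseline and arm. "All tests will be two-sided with a significance level of 0.05". The covariates that Outcome measures and the Discussion promise to take into account do not include therapist, session or center.

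**The concern.** Individual randomization makes the arms comparable at the start. It does not keep outcomes independent once treatment is delivered through shared therapists who work in one arm only. The baseline FACIT-F is completed at screening, before allocation, so therapist differences can appear only as divergence after baseline. The primary test looks for exactly that kind of divergence between the arms. Because no therapist works in both arms, therapist variation does not cancel in the comparison of arms.

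The active control is meant to equalize therapist contact on average. It does not remove variation from one therapist to the next within an arm. If that variation exists and is left out of the model, some of it is read as treatment effect: the test rejects too often under the null, and the stated power assumes more information than the data hold.

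**Working it through.** **1. The plan's own figure.** 156/(1 - 0.20) = 195, rounded up to an even 196 (98 per group). This reproduces.

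**2. The stated power, with independent patients.** The article does not say whether 8 points is the SD of a difference or a residual SD.
- SD of a difference: simulating the F1-LD-F1 interaction test (78 per arm, four time points) gives power of 0.74 if the 4-point effect grows linearly to week 20, and 0.87-0.88 if it is fully present from week 8.
- Residual SD: power is 0.44 to 0.57.

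The first reading brackets the stated 80% with no clustering term. That fits the listed inputs but does not prove what the simulations contained.

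**3. Assumptions about clustering (not in the article).** 3 to 6 completers per therapist (m), that is 78/3 = 26 down to 78/6 = 13 therapists per arm. The upper end is close to one therapist per arm in each of the 14 centers (78/14 = 5.6). The ICC of the change score is 0.02, 0.05 or 0.10.

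**4. Formulas.** Design effect DE = 1 + (m - 1) × ICC. Effective N = 156/DE. Evaluable N needed to match 156 independent patients = 156 × DE; total = that/0.8. Approximate true level of a single two-sided comparison = 2 × (1 - Φ(1.96/√DE)).

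| m | ICC | DE | Effective N | Evaluable N needed | Total N | Approximate level |
|---|---|---|---|---|---|---|
| 3 | 0.02 | 1.04 | 150 | 163 | 203 | 5.5% |
| 3 | 0.05 | 1.10 | 142 | 172 | 215 | 6.2% |
| 3 | 0.10 | 1.20 | 130 | 188 | 234 | 7.4% |
| 6 | 0.02 | 1.10 | 142 | 172 | 215 | 6.2% |
| 6 | 0.05 | 1.25 | 125 | 195 | 244 | 8.0% |
| 6 | 0.10 | 1.50 | 104 | 234 | 293 | 11.0% |

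**5. Simulated level of the planned test.** The formula is for a single change score, so the F1-LD-F1 interaction test was also simulated under the null (78 per arm, SD 12, SD of difference 8, 4,000 runs per setting, Monte Carlo error about 0.35 points). The therapist effect was either present from week 8 or grew linearly.
- No clustering: 5.3% (6,000 runs).
- Cluster sizes 1 to 4 equally likely (size-weighted mean 3): 5.0-5.6%, 6.0-6.4% and 6.6-7.3% at ICC 0.02, 0.05 and 0.10.
- m = 6: 5.2-6.1%, 6.9-7.0% and 8.0-9.1%.

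Further independent simulations of the same test for m = 3 and 6 gave values up to 7.1% at ICC 0.05 and 9.9% at 0.10. Rounded over all runs: 5-6%, 6-7% and 6-10%.

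**6. Power for a comparison that keeps its 5% level.** With 78 per arm, difference 4 and SD 8, power is 0.877 if patients are independent. Replacing the SD by 8 × √DE gives 0.865, 0.845 and 0.813 for m = 3, and 0.845, 0.798 and 0.722 for m = 6. If 156 was instead chosen to give exactly 80%, power becomes Φ((1.96 + 0.84)/√DE - 1.96): 0.78 at DE 1.04, 0.71 at 1.25 and 0.63 at 1.50.

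**The case against.** **No ICC is given, and a low one is plausible.** Sessions and exercises are standardized in both arms, eurythmy therapists are certified, and all therapists attend an introductory teaching session. Supervised time is 13 × 45 = 585 min, against 15 × 6 × 20 = 1,800 min of prescribed home training, about 75% of the total. All of this stands. A reader might infer that the standard errors are certainly too small and that the test certainly exceeds 5%. The article does not support that: it needs a positive ICC. At ICC 0.01 with sessions of four, the simulated level was 4.8-5.2%, no visible excess.

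**Shared sessions may be rare.** With even recruitment over 36 months (156 weeks) and one therapist per center and arm, 98/14 = 7 patients each treated for 20 weeks give 7 × 20/156 = 0.9 in treatment at once. This stands for same-room clustering. It does not remove clustering by therapist, which does not require patients to attend together.

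**Omitting center may offset the excess.** Randomization is stratified by center and the described model has no center term, which pushes toward conservatism. But stable center differences largely cancel in a group-by-time test: with a static center effect of SD 4 added, the simulated level at m = 6 and ICC 0.10 was still 9.1%. Only center differences in change over time could offset it. That is possible, and the article does not settle it.

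**The analysis plan may handle it.** A clustered sensitivity analysis may exist in a document not shown, and its absence from the article is not the point. The point is that the article itself fixes a two-factor primary model and reports a completed power calculation, including that "The simulations also confirmed that the power of 80% is reached in case of slight deviations from the assumptions", without naming this source of variation.

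**Group size by arm.** A reader might also infer that session sizes will differ between the arms. That is speculation: both arms follow the same range, frequency and duration.

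**Conclusion.** The point holds conditionally. Therapists are arm-specific and can be shared by patients, and neither the listed sample-size inputs nor the described primary model contains therapist or session variation. If change in FACIT-F correlates within therapist, the interaction test is anti-conservative and the power at 156 is lower than under independence.

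The excess is negligible to one point at ICC 0.02, one to two points at 0.05, and one to five points at 0.10. Power on the more favorable approximation falls below 80% only with about six patients per therapist and an ICC of 0.05 or more; if 156 has no reserve, it falls below 80% at any positive ICC. These sizes rest on assumed ICCs and an assumed 3 to 6 completers per therapist. That the power simulations left clustering out is inferred from the listed inputs, since the code is not shown. The change is worth making, but this is not a demonstrated failure of the primary test.

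**What to change.** Keep the F1-LD-F1 test as primary. Prespecify beside it a repeated-measures model on the week 8, 14 and 20 scores, adjusted for baseline, with a random therapist effect nested in arm (or cluster-robust standard errors) and small-sample degrees of freedom. Therapist should not enter as a fixed effect: with therapists nested in arm, that would absorb the treatment contrast. Require the primary conclusion to be reported together with this result.

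Therapist identity should need no new data collection. Therapists enter every session in REDCap (Session 1–session 13), and the system attaches the entering user to each data point (Confidentiality and coding). State a rule for patients who change therapist.

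In the sample-size section, restate the 80% power as conditional on no therapist clustering. Give the expected number of patients per therapist and the power over a range of assumed ICCs.

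The cost is one added model and a revised paragraph. The downsides are wider intervals in the clustered analysis, a poorly estimated therapist variance where therapists have few patients, and a lower stated power.
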